### Subjects

Subjects will have a diagnosis of spastic diplegic CP. Inclusion criteria will be: 1) age between 7 and 18 years; 2) ability to follow simple verbal directions; 3) good or fair selective motor control for at least one lower limb and 4) ability to walk independently indoors, with or without assistive devices (Levels I-III of the Gross Motor Function Classification System (GMFCS) [34]. Exclusion criteria will be: 1) orthopedic surgery, neurological surgery or baclofen pump implantation within the preceding 12 months; 2) botulinum toxin injections within the preceding three months; 3) serial casting or new orthotics within the preceding three months; 4) initiating oral medications that affect the neuromuscular system, e.g. baclofen, within the preceding three months; 5) onset of physical therapy, exercise, sport activity or change in assistive devices for walking within the preceding three months; 6) inability or unwillingness to maintain age appropriate behavior; 7) serious medical conditions such as cardiac disease, diabetes or uncontrolled seizures; 8) current participation in a fitness program that includes cardiorespiratory endurance exercise, at least one time per week and 9) significant hip, knee or ankle joint contractures preventing passive movement of the lower limbs through the pedaling cycle.

Subjects will be recruited from southern California and southwest Missouri via flyers and brochures placed in clinics and schools and by postings on disability related web sites. When a potential subject contacts the investigators, a telephone screening will be performed. Subjects meeting the inclusion and exclusion criteria assessed during the telephone screening will receive an in-person screening to determine GMFCS level and selective motor control ability. Additionally, the child will be assessed on the stationary bicycle to ensure that their lower extremity joint range of motion is sufficient to move through the pedaling cycle.

If the subject qualifies during the in-person screening, enrollment procedures will occur. An investigator will explain the informed consent, medical release, photo consent and a summary of the Health Insurance Portability and Accountability Act of 1996 (HIPAA) policy to the participants and their guardians. Testing purposes and procedures, the randomization process, potential risks and benefits for participants and responsibilities of both the participants and the research team will be discussed and questions answered. If the individual and their parent/guardian decide to proceed with enrollment, the consent form will be signed and an enrollment form, containing the subject's age and selective motor control ability, will be submitted to the PTClinResNet Data Management Center for subject randomization. Families will be notified of their child's assignment to the control or intervention group following the baseline evaluation.

### Sample size

Sixty subjects (30 cycling intervention, 30 no cycling control) will be recruited for this study. A sample size of 30 in each group will have 80% power to detect a moderate effect size of 0.7 (as well as a minimal clinically important difference) using a two group t-test with a 0.05 two-sided significance level. Power analyses were performed using joint moment data outcomes following an isokinetic strengthening intervention for children with CP [16]. A 10% subject attrition rate was factored into the analyses.

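### Thirty children per group do not give 80% power for an effect of 0.7: power is 76% with no dropout and 71% after the stated 10% attrition

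*Protocol article*

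**What the plan says.** The trial's power statement is in the protocol article, Methods/design, Sample size. It fixes enrolment: "Sixty subjects (30 cycling intervention, 30 no cycling control) will be recruited for this study". It then claims that "A sample size of 30 in each group will have 80% power to detect a moderate effect size of 0.7", and names the test: "using a two group t-test with a 0.05 two-sided significance level". The same sentence says that this effect is also a minimal clinically important difference. The section traces the calculation to joint moment data from an earlier isokinetic strengthening study and closes with: "A 10% subject attrition rate was factored into the analyses".

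The Data analyses section uses t-tests on change from baseline, or Wilcoxon rank sum tests if the data are not normal, for the primary hypotheses. It adds analysis of covariance adjusting for age group and selective motor control.

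**The concern.** The section gives everything needed to check its own figure: group size, effect size, test, significance level and attrition. Thirty per group looked too few for 80% power at 0.7 even with complete follow-up. It also looked as if nothing had been added for the attrition that the section says was allowed for, since 30 per group is both the number recruited and the number in the power claim.

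This is the only planning figure in the article, and it is tied to a difference described as clinically important. If the power is overstated, so is the protection against missing that difference, and a non-significant result could be given more weight as evidence against it than the design supports.

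**Working it through.** **Inputs, all from the Sample size section**

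- Recruited: 30 per group, 1:1, 60 in total.
- Standardized effect: d = 0.7.
- Test: two-group t-test, two-sided α = 0.05.
- Attrition: 10%, so 30 × 0.9 = 27 evaluable per group.
- Stated power: 80%.

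**Formula.** With n per group, the t statistic has 2n − 2 degrees of freedom and noncentrality d × √(n/2). Power is the probability that it exceeds the two-sided 5% critical value. The normal approximation is Φ(d × √(n/2) − 1.960).

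**Attempt to reproduce the stated 80%**

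- n = 30: df = 58, noncentrality = 0.7 × √15 = 2.711.
- n = 27: df = 52, noncentrality = 0.7 × √13.5 = 2.572.

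| Evaluable per group | Power, exact t | Power, normal approximation |
|---|---|---|
| 27 | 71.4% | 73.0% |
| 30 | 76.0% | 77.4% |
| 33 | 79.97% | 81.2% |
| 34 | 81.2% | 82.3% |

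The stated figure is not reproduced at 30 or at 27 per group by either method.

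**Sample size that would give 80%**

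- Normal approximation: n = 2 × (1.960 + 0.842)² / 0.7² = 32.04, rounded up to 33.
- Exact t: 33.02, rounded up to 34. At 33 the power is 79.97%, so 33 to 34 is a fair range.
- With 10% attrition: 33 / 0.9 = 36.7, so 37; 34 / 0.9 = 37.8, so 38. That is 74 to 76 recruited in total, against 60 planned.

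**Effect detectable with 80% power (exact t)**

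- 30 per group: 0.736.
- 27 per group: 0.777.

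**Variants that might explain the printed figure**

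- *Rounded effect size.* A value just below 0.75 would print as 0.7. At 0.7499, power is 81.5% with 30 per group but 77.2% with 27.
- *One-sided 0.05 test.* 80% power needs 26 per group, and 26 / 0.9 = 28.9, so 29 recruited. At 27 per group the power is 81.4%. This fits 30 recruits with attrition allowed for, but the section specifies a two-sided test.

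**The case against.** The strongest defence is rounding. The effect is printed to one decimal and is said to rest on earlier joint moment data, so the value used may not have been exactly 0.70. With 30 analysed per group, the effect detectable with 80% power is 0.736, which rounds to 0.7. Over the range that prints as 0.7, power at 30 per group runs from about 70% (d = 0.65) to about 81% (just under 0.75). So the 76% figure alone, with no dropout, would not prove an error. That much stands. It needs all 30 recruits to be analysed, however, and the section's last sentence says attrition was allowed for. At 27 per group no effect that rounds to 0.7 reaches 80%.

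A second defence is that the planned analysis of covariance could be more powerful than the t-test. It could, but the power claim is made for a t-test, t-tests or rank sum tests are assigned to the primary hypotheses, and no correlation is given from which to calculate a gain. The 71% is therefore the power of the t-test, not of every planned analysis.

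Third, this is described as a Phase I trial, and nowhere does the article plan to read a null result as proof of no effect. That is fair: over-reading is a risk, not something the plan commits to. It is also a reason not to ask for a larger trial. It does not make the printed figure correct.

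**Conclusion.** The statement is wrong as written. For a two-sided 0.05 two-group t-test at a standardized effect of 0.70, 60 recruits give 71.4% power after the stated 10% attrition, about 9 points below the claim. With no dropout they give 76.0%, 4 points below. The type II error at the target effect is 100 − 71.4 = 28.6%, against the 20% implied.

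These figures assume equal loss in the two groups, attrition of exactly 10% and an effect of exactly 0.70. The conclusion does not depend on the last of these: at 27 per group, any effect that rounds to 0.7 leaves power at 77% or below. Nor does it depend on the choice between exact t and normal approximation at the stated 0.7. The shortfall is moderate, but it affects the one figure on which the size of the trial rests.

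**What to change.** Replace the power sentence and the attrition sentence with one statement whose parts agree, for example:

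*Sixty children (30 per group) will be recruited. With 10% attrition, leaving 27 evaluable per group, a two-sided 0.05 two-group t-test has 71% power for a standardized difference of 0.70 and 80% power for a standardized difference of 0.78.*

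If the calculation in fact used an unrounded effect of about 0.74 and no allowance for dropout, print that effect and delete the attrition sentence; at 0.74, 30 analysed per group give 80.5%. If the sponsor wants to rely on a covariance-adjusted analysis for power, it should state the power under that model together with the assumed correlation.

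The cost is a rewording within one section, with a less favourable figure in print. Enrolment, conduct and analysis need not change. Keeping both 80% power at 0.70 and the 10% allowance would instead require 37 to 38 recruits per group.

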### Stationary bicycle

The stationary bicycle in this study was designed for rehabilitation and allows the subject to begin cycling with minimal resistance (Biodex Lower Body Cycle, Biodex Medical Systems, Inc, Shirley, New York) (Fig. 1). This bike uses a semi-recumbent design with a wide padded seat and seat belt, back support, and foot straps attached to the pedals. There are two mechanisms to provide resistance to the lower extremities during cycling: 1) standard cycling and 2) cyclocentric cycling. During standard cycling, the bicycle seat is locked in place. The exercise mode is adjustable from a front operation panel using two different options: "Aerobic exercise – constant power" or "Strengthening exercise – isokinetic". The aerobic exercise mode employs an effort level control from 1–30. The strength exercise mode uses a speed control increment from 25 to 120 degrees per minute.

Cyclocentric cycling is a unique limb-loaded feature of this stationary bicycle and its use for rehabilitation following stroke has been described by Brown and colleagues [35]. To use this feature, the seat is released and allowed to slide forward and backward along a linear track. The seat is released by pulling a handle located just below the bicycle's front panel. Up to ten tensioning cords (10 lbs of force per cord) can be attached to the base of the seat acting to pull the seat forward, thereby passively flexing the subject's lower extremities. Extension of one lower limb is necessary to resist the excessive flexion caused by the tensioning cords, and to maintain the seat within a desired range called the "cyclocentric exercise zone". This optimal forward-backward position for the seat is indicated by arrows pointing to a location within a green colored zone along the linear track located at the base of the bicycle (see Figure 1a and 1b). This zone is visible to the subject during cycling.

### Cycling intervention protocol

Thirty exercise sessions will occur over a 12-week period. The optimal frequency is three times per week over a ten-week period; however, this alternative schedule provides flexibility for vacations, illnesses or other events. Each session will last approximately 60 minutes. Subjects will be asked to wear shorts and tennis shoes during each session for comfort, safety and assessment purposes. They will receive individualized instruction for an independent self-stretching exercise program for bilateral hip flexor, knee extensor, knee flexor, and ankle plantar flexor muscles as a 5–10 minute warm-up prior to cycling. Additional muscle groups that exhibit reduced range of motion may be included in the stretching program for individual subjects. The cycling intervention will be divided into two phases: 1) Lower extremity strengthening and 2) Cardiorespiratory endurance.

#### Phase 1: lower extremity strengthening

The seat location will be adjusted to ensure a knee joint angle of between 15 and 20 degrees of flexion when the knee is maximally extended during cycling. Subjects will be instructed to hold onto the side of the seat because it is possible to slide the seat backwards by pushing with the upper extremities when using the alternate hand rest position on the front of the bicycle. Lower extremity resistance training will begin with the attachment of one tensioning cord. The seat will be released and the subject instructed to begin cycling while keeping the seat within the desired cyclocentric zone. If the subject has difficulty transferring resistance from one limb to the other, the therapist may assist by stabilizing the seat in the desired cyclocentric zone as the lower limb moves from maximum flexion into extension at the top of the pedal revolution. Difficulty during this transition results in a "jerking forward" of the seat rather than a smooth rhythmic cycling motion. If the subject continues to have difficulty with this transition, the therapist may physically assist the foot in moving forward through the top of the pedaling cycle. The subject will be instructed to avoid "locking" the knees in full extension near the bottom of the pedaling cycle, a strategy that might occur as a compensation for weakness. If this deviation persists, a physical block will be slid along the track and positioned behind the seat to prevent excessive knee extension. Once the subject is able to cycle in a smooth pattern without difficulty for ten complete pedaling revolutions, a second tensioning cord will be engaged increasing the resistance to 20 lbs. The above protocol will be repeated until the subject either cannot cycle at the next higher cord increment or the cycling pattern is not smooth. This level of resistance will be recorded as the maximum cord level for the session.

During subsequent sessions, the subject will begin with a minimum of 20 revolutions at cord levels below the previous session's maximum. They will progress to the maximum cord level, gradually increasing the number of revolutions. During each session, the minimum and maximum number of tensioning cords and the corresponding number of revolutions will be recorded. The maximum resistance possible is 10 cords, or 100 lbs of force. The total duration of this phase of the intervention is approximately 10–15 minutes.

#### Phase 2: cardiorespiratory endurance training

During the first intervention session, the subject will be instructed in the use of the Children's Effort Rating Table (CERT) [36]. The CERT uses a 1 to 10 numeric scale, with 1 corresponding to "very, very easy," to 10 corresponding to "so hard I'm going to stop." At the beginning of each intervention session, resting heart rate (HR) will be recorded after a period of quiet sitting. A target HR range of 70 to 80% maximum HR will be calculated for each session using the Karvonen Formula [37] (Target HR = [(HRmax - HRrest) × (0.70 or 0.80)] + HRrest; where HRmax = 220 - age). A sensor placed on the ear or the chest will monitor the subject's HR. The therapist will assess the radial pulse to confirm accuracy of the electronic HR monitor prior to initiating cycling. If the electronic HR monitor readout is different, adjustments of sensor placement will be made until agreement is found.

To begin the cardiorespiratory endurance phase, the limb-loading feature will be disengaged and the bike locked in a stable position. The seat will be positioned to ensure that the subject's knee joint is in 15 – 20 degrees of flexion when maximally extended. Cycling resistance will be adjusted using the "Aerobic exercise – constant power" mode. Cycling will begin at a low level and be adjusted up or down according to the subject's ability. If the subject is able to cycle for 10 consecutive minutes within the target HR range, the therapist will switch to the "Strength exercise – isokinetic" mode with a setting of 60 cycles per minute for a two-minute period, thus increasing the intensity of the resistance. The goal for the initial session is 15 minutes of cycling. A variety of motivational strategies will be used during the intervention to promote continued cycling and to increase intensity of effort. Therapists will place the HR monitor in front of the subject and encourage them to cycle faster in order to increase their HR. Additional strategies include verbal encouragement, listening to music, pretend play and counting the number of lower extremity revolutions possible while maintaining a given HR level or exercise level setting on the bicycle. The child will be asked to describe their perceived exertion throughout the cycling session using the CERT. If the HR is below target range but the subject is cycling at a high rate, the constant level resistance will be increased. If a subject expresses a high level of fatigue, or a CERT level of 9 or 10, the constant level resistance will be decreased or the subject will be instructed to slow the pedaling rate. Subjects will be encouraged to gradually increase their exercise duration to a maximum of 30 minutes over the thirty sessions. A cool-down period will occur at the end of the intervention as the subject pedals without resistance until his or her HR decreases to within 20 beats above baseline. Therapists will be provided with a worksheet to record HR and CERT levels. For each session, an intervention form will be completed containing the following information: 1) baseline HR; 2) target HR range; 3) aerobic exercise level setting; 4) the subject's typical exercise HR (TEHR); 5) duration of the TEHR; 6) time to reach TEHR; 7) total cycling duration and 8) CERT level while at TEHR. If a range of values are observed or reported for these parameters, the most representative for the session will be recorded.

### Outcome measures

#### Outcome data collection sessions

For the Los Angeles site, data collection will take place at the Division of Biokinesiology and Physical Therapy at the University of Southern California and the Francisco Bravo Medical Magnet High School Gymnasium, Los Angeles Unified School District. Missouri site data collection will take place at Missouri State University. An interpreter will be present for parents or guardians who are non-English speaking. Measurements of subject height and weight will be obtained during each session. For the control group, follow-up evaluations will be scheduled within 10–12 weeks after the baseline evaluation. For the intervention group baseline data will be collected within a one-month period prior to the initiation of intervention sessions. Follow-up data will be collected within a two-week period following the last intervention session.

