**Methods/design:**

The rationale and design of a randomized controlled trial examining the effects of a stationary cycling intervention for children with CP are outlined here. Sixty children with spastic diplegic CP between the ages of 7 and 18 years and Gross Motor Function Classification System (GMFCS) levels of I, II, or III will be recruited for this study. Participants will be randomly assigned to either an intervention (cycling) or a control (no cycling) group. The cycling intervention will be divided into strengthening and cardiorespiratory endurance exercise phases. During the strengthening phase, the resistance to lower extremity cycling will be progressively increased using a uniquely designed limb-loaded mechanism. The cardiorespiratory endurance phase will focus on increasing the intensity and duration of cycling. Children will be encouraged to exercise within a target heart rate (HR) range (70 – 80% maximum HR). Thirty sessions will take place over a 10–12 week period. All children will be evaluated before (baseline) and after (follow-up) the intervention period. Primary outcome measures are: knee joint extensor and flexor moments, or torque; the Gross Motor Function Measure (GMFM); the 600 Yard Walk-Run test and the Thirty-Second Walk test (30 sec WT).

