### Physical activity calendars

All subjects will be provided with calendars and stickers at their initial baseline evaluation to chart their daily physical activity levels throughout the 12-week intervention period. These data are a measure at the ICF level of participation and will inform the investigators of periods of illness or injury that could affect data interpretation. Activities will be classified into four different levels: high, moderate, low and bedrest. The subject will be instructed to place a sticker on each day of the calendar that corresponds to their participation in the following activity levels. A high activity level is defined as participating in activities such as running/jogging, contact sports, hiking, dancing, climbing stairs or biking for over a one-hour period. A moderate activity level is defined as participating in the above activities over a 30-minute period or activities such as swimming, skateboarding, scooter riding or walking for approximately one-hour. A low activity level indicates a sedentary day with activities such as schoolwork, television or computer games. Bedrest indicates that a child is inactive for the entire day due to illness or injury. A folder will be given to the family with calendars, written instructions, colored stickers and contact information for the investigators. Materials are available in English and Spanish. Subjects randomized to the cycling intervention group will be instructed to exclude the cycling intervention when recording their daily activity levels. They will begin calendar recording following their baseline data collection and will return them at the follow-up evaluation session.

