### Data analyses

Student t-tests (if normally distributed) or Wilcoxon rank sum tests (if non-normal) will be used to contrast the change from baseline within and between the intervention and control groups for the primary hypotheses. Analysis of covariance procedures will be used to contrast changes adjusting for selective voluntary motor control (good versus fair) and age group (younger, 7–11 years) and (older, 12 – 18 years) for primary outcome measures.

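### Follow-up is timed by different rules in the two arms, so change from baseline is measured over a planned interval about three weeks longer in the cycling arm (midpoints 14 versus 11 weeks)

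*Protocol article*

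**What the plan says.** The timing rules are in the protocol article under Outcome data collection sessions. For controls: "For the control group, follow-up evaluations will be scheduled within 10–12 weeks after the baseline evaluation". For the cycling arm there are two rules, one at each end of training: "For the intervention group baseline data will be collected within a one-month period prior to the initiation of intervention sessions", and "Follow-up data will be collected within a two-week period following the last intervention session".

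The length of training is given under Cycling intervention protocol: "Thirty exercise sessions will occur over a 12-week period", with the remark that "The optimal frequency is three times per week over a ten-week period". The abstract puts it as "Thirty sessions will take place over a 10–12 week period".

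Under Data analyses, t-tests or rank sum tests are to "contrast the change from baseline within and between the intervention and control groups for the primary hypotheses". The analysis of covariance adjusts for selective motor control and age group. Neither analysis, as stated, refers to the time between the two assessments. The article does not state the cycling arm's total interval.

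**The concern.** The control window equals the length of the training period alone. It leaves no room for the lead-in before the first session or the delay after the last one, both of which the cycling arm is allowed. A cycling child has a control-length interval only if training starts almost at once after baseline and follow-up comes almost at once after training. Some lead-in is likely, because families learn the allocation only after the baseline evaluation and the sessions are held in community clinics.

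The outcome is change from baseline in children aged 7 to 18. Anything that moves torque, gross motor score or walking performance with time alone has longer to act in one arm. Randomization balances the children, not a measurement schedule that differs by arm. A bias of this kind does not shrink as the sample grows, and it is part of the plan even when every visit is on time.

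**Working it through.** **Inputs (protocol article)**

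- Control interval: 10 to 12 weeks from baseline (Outcome data collection sessions).
- Cycling lead-in, baseline to first session: 0 to 1 month (same section). Taken as 30 days, 30/7 = 4.29 weeks; a 28- to 31-day month gives 4.0 to 4.4 weeks.
- Cycling training period: 10 to 12 weeks (abstract; Cycling intervention protocol).
- Cycling delay, last session to follow-up: 0 to 2 weeks (Outcome data collection sessions).

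The article states no total interval for the cycling arm, so there is no figure to reproduce.

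**Step 1. Intervals.** Cycling interval = lead-in + training + delay.

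| | Cycling (weeks) | Control (weeks) | Difference |
|---|---|---|---|
| Minimum | 0 + 10 + 0 = 10 | 10 | 0 |
| Midpoint | 2.14 + 11 + 1 = 14.1 | 11 | 3.1 |
| Maximum | 4.29 + 12 + 2 = 18.3 | 12 | 6.3 |

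The cycling maximum is 18.0 to 18.4 weeks depending on the month. On the preferred 10-week schedule it is 4.29 + 10 + 2 = 16.3 weeks. At the midpoints the cycling interval is 14.1/11 = 1.29 times the control interval.

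**Step 2. Overlap of the windows (assumption: each component independent and uniform over its allowed range).** A cycling interval stays at or below 12 weeks only if lead-in, training time beyond 10 weeks, and delay sum to at most 2 weeks. That probability is (2³/6)/(4.29 × 2 × 2) = 1.33/17.1 = 0.08, so about 92% of cycling intervals would exceed 12 weeks. With training fixed at 10 weeks it is (2²/2)/(4.29 × 2) = 2/8.57 = 0.23, so about 77% would. No control seen on schedule exceeds 12 weeks.

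**Step 3. Illustrative size on torque (assumption: torque grows by a fraction g a year; the article gives no rate).** Excess change = (1 + g)^(w/52) − 1, with w the gap in weeks.

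- Midpoint gap, w = 3.1: g = 0.10 gives 0.6%; g = 0.20 gives 1.1% of baseline torque.
- Gap between the maxima, w = 6: g = 0.10 gives 1.1%; g = 0.20 gives 2.1%.

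**Step 4. The same on a standardized scale (assumption: drift of 0.01 to 0.05 SD of change per week).** A gap of 3.2 weeks (14.2 versus 11, using an average calendar month) gives 3.2 × 0.01 = 0.03 SD to 3.2 × 0.05 = 0.16 SD. With 30 per arm and a two-sided 5% t-test, the false-positive rate rises to between about 5.2% and 9.4%. The Sample size section plans for an effect of 0.7 SD.

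**The case against.** The strongest reply is that the effect is small and its direction is not established. The assumed drift gives 0.03 to 0.16 SD against a planned effect of 0.7, and the article describes no natural course for torque, gross motor function or walking in these children. The same rules also allow up to two weeks without training before follow-up, which could shrink a real training effect. Height and weight are measured at each data collection session, so growth is at least recorded. All of this stands. It limits the size and certainty of the bias, but does not remove the difference in schedule.

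A second reply is that the statistical analysis plan, not shown here, may adjust for the interval. That would help little. With most cycling intervals likely to exceed 12 weeks and no on-schedule control doing so, interval is nearly confounded with arm, and adjustment would rest on extrapolation. The remedy lies in the scheduling.

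Some stronger readings are tempting but not supported:

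- **An 8-week gap.** This pairs the longest cycling interval with the shortest control interval: two individual children, not a difference between arms.
- **Evaluators are unblinded.** An on-schedule interval above 12 weeks can belong only to the cycling arm, but an evaluator would have to know the baseline date. The article neither says so nor rules it out, and it does specify blinded evaluators.
- **Activity calendars stop too early.** Children are to "chart their daily physical activity levels throughout the 12-week intervention period", starting after baseline and returning the calendars at follow-up. Nothing caps recording at 12 weeks from baseline; at most the wording is unclear for a child who starts late.
- **Children who stop cycling early are measured early.** The article does not say how they are scheduled.

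**Conclusion.** The point holds as a design weakness that should be fixed. Followed exactly, the plan compares change over 10 to about 18 weeks in one arm with change over 10 to 12 weeks in the other: about 3 weeks apart at the midpoints and about 6 weeks at the maxima. These figures follow from the article's own windows.

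The resulting bias is less certain. That it favours cycling assumes that outcomes rise with growth or time. That it is modest, about 0.6% to 1.1% of baseline torque at the midpoint gap, assumes 10% to 20% growth a year. Neither assumption comes from the article. A reader might infer that the trial could show a benefit from timing alone; the illustrative figures do not support that unless drift is large.

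**What to change.** Keep the cycling arm's end-of-training assessment. Schedule each control's follow-up at the same planned baseline-to-follow-up interval as the cycling arm, for example matched to a cycling child in the same age and motor-control stratum, about 14 weeks on average.

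Shortening the permitted gap between baseline and the first session, alone or in combination, also narrows the difference. It does not close it without some change to the control window: even with no lead-in, the cycling interval would be 10 + 0 = 10 to 12 + 2 = 14 weeks (midpoint 12), against 10 to 12 (midpoint 11).

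A single wide window counted from baseline regardless of training is less attractive. With a window to 18 weeks, a child who starts at once and finishes in 10 weeks could be tested up to 18 − 10 = 8 weeks after training ends.

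Record the actual interval for every child and report its distribution by arm.

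The cost is a revised scheduling rule: controls are seen a few weeks later, or baseline visits are booked more tightly against the first session. No visits are added. As a secondary gain, equal windows remove elapsed time as a possible clue to allocation, should evaluators know the baseline date.
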